**Figure 1 F1:**
[figure not shown]
Study flow diagram. ABPM, ambulatory BP monitoring; ACEi, ACE inhibitor; ARB, angiotensin receptor blocker; BP, blood pressure; CCB, calcium channel blocker; mRS, modified Rankin Scale; TIA, transient ischaemic attack.

### Patient and public involvement

The trial was conceived and designed without the involvement of patients or members of the public.

### Trial participants

All adult patients with clinically definite first-ever ischaemic stroke or TIA within 7 days of onset will be considered for the trial.

### Inclusion criteria

Age >18 years.Patients with first-ever clinically definite TIA and ischaemic stroke (NIHSS <10).Within 7 days of symptom onset (this criterion was initially within 72 hours of symptom onset, but was altered with a substantial amendment to the protocol to try and improve recruitment).Casual BP >130/80 mm Hg on repeat measurements.Ability to comply with randomly assigned BP-lowering regime and BP measurements.Able to understand written and verbal English.Able to give informed consent.Willing to allow his or her general practitioner (GP) and consultant, if appropriate, to be notified of participation in the study.

### Exclusion criteria

The participant may not enter the trial if any of the following apply:Known definite contraindication to BP-lowering regime or therapeutic agents.Swallowing difficulties which would preclude the taking of oral medication.Definite indication for BB, CCB, ACEI or ARB therapy.Significant prestroke dependency (mRS >3).Coexisting life-threatening condition with life expectancy <3 months.Previous participation in this trial or current participation in another investigational drug trial.Atrial fibrillation.Female participants who are pregnant, lactating or planning pregnancy during the course of the study.Unable to understand written and verbal English.Cannot give informed consent.

### Identification of participants

Patients with first-ever TIA and minor ischaemic stroke referred to and assessed by the inpatient and/or outpatient stroke services at three centres within 7 days of symptom onset will be identified by the treating clinician and/or the research team. If the patient provides verbal consent to be considered for the study then their medical records will then be assessed against the study inclusion and exclusion criteria. Patients known to be hypertensive and on treatment prior to their cerebrovascular event should have their antihypertensive medications suspended at admission, in keeping with standard practice at the recruiting centres, unless there is a specific indication for them to continue. Where treatment is suspended and the patient is willing to be considered for the trial then they are potentially eligible for inclusion provided other inclusion/exclusion criteria are not violated. Once a potential participant has been confirmed to be eligible then research staff will approach the individual to discuss the study in more detail, provide a participant information sheet and seek written informed consent.

### Obtaining informed consent

The participant must personally sign and date the latest approved version of the informed consent form, countersigned by a delegated member of the research team, before any study-specific procedures are performed. Written and verbal versions of the participant information sheet and informed consent form will be presented to the participants detailing no less than: the exact nature of the study; the implications and constraints of the protocol; and the known side effects and any risks involved in taking part. It will be clearly stated that the participant is free to withdraw from the study at any time for any reason without prejudice to future care, and with no obligation to give the reason for withdrawal. The person who obtained the consent must be suitably qualified and experienced, and authorised to do so by the chief/principal investigator as detailed on the delegation of authority and signature log for the study. The original signed form will be retained at the study site within the investigator site file. A copy of the signed informed consent will be given to participants and a copy retained in their medical notes.

### Randomisation

After the baseline assessments eligible patients will be randomised using a computer-generated protocol, in blocks of 4, to a dihydropyridine CCB or ACEI/ARB-based regime. The study treatment will be dispensed at the baseline visit, but treatment will not be commenced within 48 hours of the qualifying event in keeping with current recommended practice. The actual therapeutic agent used will be at the discretion of the treating clinician, but dictated by the class of therapy that the participant is assigned to. Prescription of the medication will be done by the treating clinician and the initial supply will be dispensed by the treating hospital or community pharmacy in accordance with the hospital’s policy for providing discharge or outpatient medication. Further supplies will be provided by the participant’s GP. Unblinding will not be necessary as there is an open-label study design.

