**Methods:**

150 adult patients with first-ever ischaemic stroke or TIA who require antihypertensive therapy for secondary prevention will be recruited within 7 days of the event from stroke services across three sites. After baseline assessments they will be randomly assigned to treatment with a calcium channel blocker or ACE inhibitor/angiotensin receptor blocker-based regimen and followed up for a period of three months.

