## Methods and analysis

### Study overview

This study is a randomised, multicentre, open-label parallel group study to determine the feasibility of conducting such a trial in a National Health Service (NHS) setting to investigate class effects of antihypertensive medications on BPV in patients with acute ischaemic stroke or TIA. The aim is to evaluate barriers to recruitment, identify potential safety issues and demonstrate that it is possible to detect differences in BPV over the proposed study duration. We also hope to investigate the potential therapeutic benefit of targeting BPV after acute ischaemic stroke/TIA in terms of functional outcome in order to help estimate the necessary sample size for a future definitive trial. A summary of the study design is provided in figure 1. Recruitment commenced in January 2018 and is ongoing. The trial was prospectively registered: International Standard Randomised Controlled Trial Number 10853487.

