### Sample size calculation

A feasibility study of 150 patients (64 patients per group with a 15% dropout rate) will have an 80% power at the 5% significance level of detecting an 8 mm Hg difference in systolic BPV between the CCB and ACEI/ARB-based regimes, assuming a mean systolic BPV SD of 14.97 mm Hg in the CCB arm and 16.95 mm Hg in the ACEI/ARB arm.^37^

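### A fixed block of 4, published during open-label recruitment, lets staff who see whole blocks foresee up to a third of allocations with certainty; on one list shared by three sites the share is lower

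*Protocol article*

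**What the plan says.** Under Randomisation the protocol article states that "eligible patients will be randomised using a computer-generated protocol, in blocks of 4, to a dihydropyridine CCB or ACEI/ARB-based regime". One block size is given. The same section adds that "Unblinding will not be necessary as there is an open-label study design".

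Study overview reports that "Recruitment commenced in January 2018 and is ongoing", so the block size became public during enrolment.

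On who is involved:

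- Identification of participants says that candidates "will be identified by the treating clinician and/or the research team".
- Randomisation says that "Prescription of the medication will be done by the treating clinician".
- The abstract says that patients "will be recruited within 7 days of the event from stroke services across three sites".

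The article does not say whether the blocks run within site or along one common list. The 1:1 ratio is inferred from the equal group sizes under Sample size calculation ("64 patients per group with a 15% dropout rate").

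**The concern.** In an open-label trial the people who recruit can learn what earlier patients received. If they also know that every block holds two patients per arm and no other size is used, the end of each block is determined by its beginning. The treating clinician may both put patients forward and prescribe the assigned class, so one person may see past allocations and influence who enters next.

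The article leaves room to act on an expected arm. The inclusion criteria ask for a judgement on whether the patient can comply with the assigned regimen. The exclusion criteria include contraindications to the agents and definite indications for particular drug classes. The 7-day window gives some freedom over timing. Consent and baseline assessment come before randomisation, but the choice of whom to approach comes before both.

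The between-arm BPV difference is the quantity on which the sample size rests, and Study overview intends the functional outcome data to help size a definitive trial. Under Exploratory analyses, the BPV model adjusts only for baseline BP and for stroke versus TIA, and mRS and MoCA are compared without adjustment. Selection on other patient features would pass into these comparisons.

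**Working it through.** **Inputs.** Block size 4, open label and three sites are stated in the article. Two patients per arm in each block is inferred. The site splits below are assumptions.

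**The article's own figure.** It states no predictability figure; the sample size is used here only to turn shares into counts. The pooled SD is √((14.97² + 16.95²)/2) = 15.99. For a difference of 8 mm Hg at two-sided 5% and 80% power, the t-test needs 63.7, so 64 per group. Then 128/0.85 = 150.6, against 150 stated. The figure reproduces and is not in dispute.

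**Full view of the block.** The six equally likely blocks are AABB, ABAB, ABBA, BAAB, BABA and BBAA, which give 24 positions.

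- Position 4 is always determined: 6 positions.
- Position 3 is determined when the first two match (AABB, BBAA): 2 positions.
- Certain share: (6 + 2)/24 = 8/24 = 33.3%, and 150 × 1/3 = 50 patients.

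If staff always guess the arm with more places left, the chance of being right at positions 1 to 4 is 1/2, 2/3, 2/3 and 1. The mean is (17/6)/4 = 17/24 = 70.8%, against 50% with no foreknowledge.

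**One unstratified list, staff seeing only their own site but knowing the list position.** Let p be the site's share of recruitment. An allocation is certain once two earlier patients in the block, both at that site, received the same arm.

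- Position 3: p² × 1/3.
- Position 4: p³ + 3p²(1 − p) × 1/3 = p².
- Mean over four positions: (p²/3 + p²)/4 = p²/3.
- Averaged over sites: Σp³/3.

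| Assumed split | Σp³/3 | Simulated, 150 patients | Best guess right (simulated) |
|---|---|---|---|
| Three equal sites | (3 × 1/27)/3 = 3.7% | 3.6% | 56.9% |
| 80/10/10 | (0.512 + 0.001 + 0.001)/3 = 17.1% | 16.9% | 62.9% |

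The simulated shares are slightly lower because 150 is not a multiple of 4 and the last block is incomplete. If list position is also unknown, single-site staff cannot tell which of their patients share a block, and essentially nothing is certain.

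**Effect of varying the block size.** With blocks of 4 and 6 mixed at random, and staff who see every allocation and know the two possible sizes, simulation gives 5.5% certain (from 33.3%) and 69.2% of best guesses right (from 70.8%).

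**The case against.** One third is reached only if staff see every earlier allocation in the block and know where it starts. The article states neither. It describes one sequence, mentions no stratification by centre, and recruits from inpatient and outpatient services at three centres. A clinician who prescribes for one patient does not thereby know the whole sequence. Stratification and concealment are details that a condensed article commonly leaves to the full protocol. This stands: one third is an upper bound. It does not dispose of the point, because the single block size, the open label and the disclosure during recruitment are all stated.

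The exclusions remove the clearest reasons to prefer an arm, and Strengths and limitations already concedes that open label could bias these secondary comparisons. The first part narrows the scope for steering without closing it. The second does not mention predictable allocation, which acts before randomisation and not through open-label follow-up.

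The remedy is also modest, since best guessing hardly changes. That is correct and belongs in the account of the fix.

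A reader might infer that recruiters can foresee a third of allocations whatever the arrangement, that the primary feasibility outcome is biased, or that selection has occurred. The documents support none of these. The first needs conditions that the article does not state. The primary outcome consists of overall recruitment and retention with reasons for non-inclusion; foreknowledge acts mainly between arms, and at most could colour some of the recorded reasons. Nothing in the article shows that anyone steered entry.

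**Conclusion.** The point holds as a conditional weakness in allocation concealment. With a full view of the block, up to 33.3% of allocations are certain and 70.8% can be guessed. On one shared three-site list, certainty runs from essentially none (position unknown) to about 4% (equal sites, position known) and about 17% (80/10/10, position known). The splits, and staff knowledge of list position, are assumptions.

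The BPV, mRS and MoCA comparisons between arms are exposed. These are secondary or exploratory, but the first carries the sample size and the functional data are meant to inform a later trial. Recruitment and retention rates are little affected. The size of any resulting bias cannot be derived from the article.

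**What to change.** For patients still to be randomised, replace the fixed block of 4 with randomly varying block sizes that sites are not told. Keep whatever stratification is now in place. Do not newly add blocking within centre: if the present list is common to all sites, that would show each site its own complete blocks and could raise predictability. In the report, compare baseline features by arm for patients randomised under the fixed block.

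The cost is a new list, a minor amendment and a slightly larger possible imbalance in numbers: with blocks of 4 and 6, an unfinished block can leave a difference of up to 3 patients per list instead of 2. The gain is mainly the loss of certainty. The number of patients still to be randomised is not given, so the overall benefit cannot be quantified.

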### Interventions to be measured

#### Routine clinical data

The following routine clinical information and investigation results will be obtained from the medical notes and by participant interview:Demographics (including age, sex, ethnicity, height and weight, smoking and alcohol habits).Medical history and family history of cardiovascular disease.Concomitant medications.NIHSS.mRS (including premorbid mRS).Oxford Community Stroke Project and Trial of ORG 10172 in Acute Stroke Treatment classification.Laboratory tests (including full blood count, clotting, urea, electrolytes, creatinine, estimated glomerular filtration rate, total cholesterol and random glucose).12-lead ECG (±24 hours ECG if performed).Imaging investigations (including neuroimaging (CT or MRI), carotid ultrasound and cardiac echocardiography where applicable).

#### BP measurements

Baseline casual BP will be calculated as a mean of two sets of three supine brachial BP readings taken 10 min apart using a UA767 BP monitor (referred to as enhanced casual BP).

Three consecutive periods of 10 min beat-to-beat non-invasive BP monitoring in the supine position using the middle finger of the non-hemiparetic hand will be recorded with a Finometer device. The servo adjust mechanism of the Finometer will be switched off during the recording period, but applied at 10 min intervals during the monitoring period.

Daytime ambulatory BP monitoring (ABPM) will be performed using a SpaceLabs 90207 monitor, programmed to measure BP at 20 min intervals. Daytime is defined as between 07:00 and 22:00 hours.

#### Cognitive testing

A battery of cognitive tests will be performed. This will include the MoCA screening test which is established for use after cerebrovascular events, augmented with the Albert’s line test for inattention, the Motor Neuron Disease Behavioural Instrument for frontal cognitive symptoms and the Geriatric Depression Scale to exclude significant concurrent anxiety/depression.

### Follow-up assessments

These will be undertaken at day 21 (±7 days) and day 90 (±14 days) in the trial centre or where the patient is resident at the time (including the hospital ward, rehabilitation facility or their own home). Interventions that will repeated at these follow-up visits are summarised in table 1. Additional follow-up interventions to assess the trial feasibility and safety will include assessment of treatment compliance using a self-reported questionnaire and tablet count (with compliance defined as ≥80%), and assessment of any side effects and SAEs. Patients randomised to the ACEI/ARB arm will have repeat renal function blood tests at the first follow-up visit in line with standard practice to ensure their safety. In those patients failing to reach casual supine/sitting BP target of <130/80 mm Hg, the medical assessor at the follow-up visit will advise about altering BP-lowering treatment and this will be communicated to the participant’s GP. The first-line change will be to increase the study regime medication (ie, CCB or ACEI/ARB) to twice the starting dose. If the patient is on the maximum dose of the study regime medication already, then the second-line change will be to add a thiazide-like diuretic. If a third-line change is required then spironolactone or an alpha-blocker will be added to the combination of study medication and thiazide-like diuretic. After the second follow-up visit ongoing management of the patient’s BP will be taken over by the GP.

**Table 1 T1:** Summary of trial procedures

Procedures	Visits			
	Screening	Baseline	21 (±7) days	90 (±14) days
Informed consent		**X**		
Demographics		**X**		
Medical history		**X**		
Concomitant medications		**X**	**X**	**X**
ECG		**X**		
Clinical investigation results (bloods tests, CT/MRI scan results)		**X**		
Eligibility assessment	**X**			
Randomisation		**X**		
Dispensing of study drugs		**X**		
Treatment compliance			**X**	**X**
Blood test for renal function in ACEI/ARB group			**X**	
NIHSS		**X**	**X**	**X**
mRS		**X** *	**X**	**X**
MoCA		**X**		**X**
Albert’s line test		**X**		**X**
MiND-B		**X**		**X**
GDS		**X**		**X**
Enhanced casual BP		**X**	**X**	**X**
Beat-to-beat BP measurements		**X**	**X**	**X**
Daytime ABPM		**X**		**X**
SAEs			**X**	**X** †

*Including premorbid mRS.

†SAEs at day 90 followed up until resolution.

ABPM, ambulatory BP monitoring; ACEI, ACE inhibitor; ARB, angiotensin receptor blocker; BP, blood pressure; GDS, Geriatric Depression Scale; MiND-B, Motor Neuron Disease Behavioural Instrument; MoCA, Montreal Cognitive Assessment; mRS, modified Rankin Scale; NIHSS, National Institutes of Health Stroke Scale; SAE, serious adverse event.

### Outcome measurements

#### Primary feasibility outcome measure

Recruitment and retention rates at 3 months from the screening and management logs, and reasons for ineligibility or non-inclusion of those screened but not recruited.

#### Secondary feasibility outcome measures

Changes in BPV from baseline to 21 (±7) days and 90 (±14) days by treatment arm.Proportions of participants achieving ≥80% treatment compliance by treatment arm.Treatment discontinuation rates.Completion and failure rates of BPV measurements at 21 (±7) days and 90 (±14) days.SAE rates by treatment arm.

#### Exploratory outcome measures

mRS at 90 (±14) days by treatment arm.mRS at 21 (±7) days by treatment arm.NIHSS at 21 (±7) days by treatment arm.Differences in mean BP at 21 (±7) days and 90 (±14) days by treatment arm.Differences in BPV at 21 (±7) days and 90 (±14) days by treatment arm.Differences in MoCA score at 90 (±14) days by treatment arm.

### Sample size calculation

A feasibility study of 150 patients (64 patients per group with a 15% dropout rate) will have an 80% power at the 5% significance level of detecting an 8 mm Hg difference in systolic BPV between the CCB and ACEI/ARB-based regimes, assuming a mean systolic BPV SD of 14.97 mm Hg in the CCB arm and 16.95 mm Hg in the ACEI/ARB arm.^37^

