#### Assessment of the intervention

Compliance with the intervention will be assessed by the proportion of participants who achieve ≥80% adherence to the trial medication and the proportion of participants who have all BP measurements recorded successfully.

The feasibility of detecting changes in BPV will also be assessed. Within-individual systolic, diastolic and mean BPV will be expressed as the SD, coefficient of variation, average real variability and variation independent of the mean calculated from all BP measurements: enhanced casual, beat-to-beat measurements (each 10 min recording and the total 30 min recording), and daytime ABPM.^42^ Changes in within-individual BPV from baseline to the follow-up time points will be analysed using a general linear model. The size of the mean difference will be estimated for each approach and compared to select the most appropriate measure for a future study.

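### The 80% power for an 8 mm Hg difference in systolic BPV is unsupported: the two planning figures are used as between-patient SDs of BPV but read most naturally as mean BPV levels

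*Protocol article*

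**What the plan says.** Under Sample size calculation, the protocol article plans "150 patients (64 patients per group with a 15% dropout rate") and states that this "will have an 80% power" at the 5% level of "detecting an 8 mm Hg difference in systolic BPV between the CCB and ACEI/ARB-based regimes". The inputs are given as "assuming a mean systolic BPV SD of 14.97 mm Hg in the CCB arm and 16.95 mm Hg in the ACEI/ARB arm", cited to reference 37. Rationale for the study describes that reference as a systematic review and meta-analysis of drug-class effects on BPV, and anticipates lower BPV on CCBs and higher BPV on ACEI/ARBs.

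Assessment of the intervention defines the outcome: "Within-individual systolic, diastolic and mean BPV will be expressed as the SD", and also as three other indices, each calculated from casual, beat-to-beat and daytime ambulatory readings. Exploratory analyses then regresses each patient's BPV on treatment arm in a general linear model, adjusting for baseline BP and diagnosis.

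Sample size calculation does not say which BPV index or measurement method it is for, and the article gives no other SD.

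**The concern.** When the outcome is itself an SD, two different quantities can be called its SD. One is the level of BPV: the average, over patients, of each patient's own SD of systolic pressure. The other is the spread of BPV: how much that within-patient SD differs from one patient to the next. A comparison of mean BPV between arms needs the spread. The wording, the cited source and the direction of the two figures all suggest that the article supplies the level and the calculation uses it as the spread.

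This matters for two reasons. The paragraph is the only justification the article gives for 150 patients. The trial also aims to show that differences in BPV can be detected over the study period and to choose a BPV measure for a definitive trial. If the inputs are levels, a reader cannot tell which BPV difference this trial can detect, and an 8 mm Hg target with an SD near 16 mm Hg could be taken forward as a benchmark without foundation.

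**Working it through.** **Inputs.** From Sample size calculation: difference 8 mm Hg; figures 14.97 (CCB) and 16.95 (ACEI/ARB); "80% power at the 5% significance level"; 64 per group; 15% dropout; total 150. Sidedness is not stated. Randomisation is "in blocks of 4, to a dihydropyridine CCB or ACEI/ARB-based regime"; equal allocation is taken from the equal group sizes.

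**Step 1. Reproduce the plan's figure.** Enter the two figures as between-patient SDs.

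- Pooled SD = √[(14.97² + 16.95²)/2] = 15.99.
- Standardised difference = 8/15.99 = 0.50.
- Normal approximation, two-sided: n per arm = 2 × (1.960 + 0.842)² × 15.99²/8² = 62.7, so 63.
- Noncentral t: 79.6% power at 63 per arm and 80.2% at 64.
- Dropout: 128/0.85 = 150.6, against 150 stated.
- A one-sided 5% test would need 50 per arm, which does not match.

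The arithmetic is sound, and it shows how the two figures were used.

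**Step 2. What the figures appear to be.** Four points in the article favour levels:

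1. The phrase describes a mean BPV SD for each arm. With BPV expressed as a within-patient SD, that is naturally the average BPV in the arm.
2. The source is described as an analysis of class effects on BPV.
3. CCB is below ACEI/ARB, the direction the rationale expects of BPV itself.
4. No BPV level is stated anywhere else, although a source on class effects would be expected to supply one.

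**Step 3. What follows if they are levels.**

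- Implied class difference: 16.95 − 14.97 = 1.98 mm Hg.
- Target relative to that difference: 8/1.98 = 4.0 times.
- Target relative to the level: 8/16.95 = 47% and 8/14.97 = 53%, about half.
- The between-patient SD of BPV is missing, so no single corrected power or sample size can be calculated.

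**Step 4. Range over the missing SD.** The SDs below are assumptions; the article gives none. Power is from the noncentral t, two-sided 5%, 64 per arm. The detectable difference is 0.50 × SD. The n per arm is from the normal approximation.

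| Assumed between-patient SD of BPV (mm Hg) | Detectable at 80% power (mm Hg) | Power for 8 mm Hg | Power for 1.98 mm Hg | n per arm, 80% power for 1.98 mm Hg |
|---|---|---|---|---|
| 4 | 2.0 | >99% | 79% | 65 |
| 6 | 3.0 | >99% | 46% | 145 |
| 8 | 4.0 | >99% | 28% | 257 |
| 10 | 5.0 | >99% | 20% | 401 |

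The stated 80% for 8 mm Hg arises only when the SD is about 16 mm Hg.

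**The case against.** The strongest reply is that nothing is miscalculated and that the phrase, though loose, can be read as the SD of BPV, which is how the calculation uses it. On that reading 64 per arm is correct. Only the cited source can settle which statistic was reported, and it is not available here. This stands: the figures cannot be declared levels as a fact, only as the more likely reading of the text.

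It is also fair that the primary objective is feasibility, that treatment effects on BPV are secondary or exploratory, and that the trial will produce its own estimates for each BPV approach, so a later trial need not inherit 8 mm Hg. This lowers the severity. It does not make the power statement supported.

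A reader might infer that the trial is underpowered for its stated target. The documents do not support that: over the assumed SDs of 4 to 10 mm Hg, power for 8 mm Hg is above 99%, so the 80% would be too low for that target. A reader might also combine the 1.98 mm Hg difference with the pooled SD of 15.99 and conclude that power is very poor. That mixes two incompatible readings: if the figures are levels, 15.99 is not the between-patient SD; if they are SDs, 1.98 is not the expected difference.

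Finally, one might argue that a non-negative index with an SD near 16 mm Hg would be too skewed for this formula. That depends on a mean the article does not give, and with 64 per arm a comparison of means tolerates a fair amount of skew. The point does not rest on it.

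**Conclusion.** The concern holds as a matter of what the inputs mean, not of arithmetic. The 80% power for 8 mm Hg depends on treating 14.97 and 16.95 mm Hg as between-patient SDs of BPV, while the article's wording, its definition of BPV and its description of the source indicate that they are most likely mean BPV levels. On that reading the power claim is unsupported. It may be far exceeded for 8 mm Hg, while for the 1.98 mm Hg contrast in the plan's own figures it runs from 79% down to 20% over assumed SDs of 4 to 10 mm Hg.

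What 64 evaluable patients per arm deliver on either reading is 80% power for a standardised difference of 0.50. The conclusion rests on the levels reading, which needs checking against the source, and the size rests on the assumed range of SDs. Severity is moderate.

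**What to change.** Keep the sample size at 150 and make these changes to the sample size paragraph:

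1. Check in the cited source whether 14.97 and 16.95 mm Hg are BPV levels or SDs of BPV, and say which.
2. Name the one systolic BPV index and measurement method to which the calculation applies.
3. If the figures are levels, withdraw the claim of 80% power for 8 mm Hg. State instead that 64 evaluable patients per arm give 80% power, two-sided 5%, for a standardised difference of 0.50 in the named measure.
4. Add a short table of detectable mm Hg differences over a range of between-patient SDs, set against the 1.98 mm Hg contrast. Recruitment is under way, so the baseline SD of BPV, pooled over arms and without reference to allocation, can inform the range.
5. If the figures prove to be SDs of BPV, keep the calculation, reword the phrase so that it cannot be read as a level, and give the reason for choosing 8 mm Hg.

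The cost is one reworded paragraph, one small table and a summary of baseline data already being collected. No extra patients are needed, and the conduct of the trial and its primary feasibility outcome do not change.
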